## Abstract

Background: Acute myocardial infarction (AMI) remains a major cause of death worldwide. Survivors of AMI are particularly at high risk for additional cardiovascular events. Consequently, a comprehensive approach to secondary prevention is necessary to mitigate the occurrence of downstream complications. This may be achieved through a multiparametric tailored risk stratification by incorporating clinical, laboratory and echocardiographic parameters. Methods: The ‘‘CLEAR-AMI Study’’ (ClinicalTrials.gov Identifier: NCT05791916) is a non-interventional, prospective study including consecutive patients with AMI without a known history of coronary artery disease. All patients satisfying these inclusion criteria are enrolled in the present study. The rationale of this study is to refine risk stratification by using clinical, laboratory and novel echocardiographic biomarkers. All the patients undergo a comprehensive transthoracic echocardiographic assessment, including strain and myocardial work analysis of the left and right heart chambers, within 48 h of admission after coronary angiography. Their laboratory profile focusing on systemic inflammation is captured during the first 24 h upon admission, and their demographic characteristics, past medical history, and therapeutic management are recorded. The angioplasty details are documented, the non-culprit coronary lesions are archived, and the SYNTAX score is employed to evaluate the complexity of coronary artery disease. A 24-month follow-up period will be recorded for all patients recruited. Conclusion: The ‘‘CLEAR-AMI” study is an ongoing prospective registry endeavoring to refine risk assessment in patients with AMI without a known history of coronary artery disease, by incorporating echocardiographic parameters, biochemical indices, and clinical and coronary characteristics in the acute phase of AMI.

## 1. Introduction

Despite ongoing advances in interventional management for patients with acute myocardial infarction (AMI), they continue to exhibit a substantial risk for cardiovascular complications [1]. Patients with AMI present at various clinical stages and suffer from myocardial damage and systemic inflammation to different extents. An advanced clinical stage indicates poorer prognosis in the acute phase and raises the risk for future cardiovascular complications, rehospitalization and death [2,3].

The inflammatory response in patients with AMI emerges shortly after reperfusion and peaks within the initial days following revascularization [4]. Inflammatory processes play a significant role in the pathophysiology of left ventricular (LV) remodeling and cardiac repair mechanisms, reflecting not only the extent of myocardial damage but also the vulnerability of individual lesions in patients with AMI [4,5,6].

Echocardiography is the mainstay imaging modality for evaluating the LV systolic function after revascularization in patients with AMI. LV ejection fraction (LVEF) is the most widely utilized index of systolic function in clinical practice [7]. However, it merely represents LV volumetric changes per cardiac cycle, which may not reflect accurately the post-AMI myocardial damage. Echocardiographic LV global longitudinal strain (GLS) has demonstrated superior predictive value to LVEF, in the short-term post AMI [8,9]. However, GLS does not account for LV dyssynchrony or LV afterload, which may be impaired after AMI. Myocardial work has been proposed as a novel echocardiographic parameter, which accounts for intrinsic myocardial function, dyssynchrony and the loading conditions [10,11].

The utilization of risk scores for early risk stratification and prognosis in patients with AMI is advocated in the current guidelines [2]. The Global Registry of Acute Coronary Events (GRACE) and Thrombolysis in Myocardial Infarction (TIMI) risk scores are employed to evaluate risk stratification post-AMI. Nevertheless, these scores primarily depend on clinical factors and standard biochemical indices without accounting for the LV myocardial damage and the inflammation burden [12]. Additionally, the Synergy Between Percutaneous Coronary Intervention with Taxus and Coronary Artery Bypass Graft Surgery (SYNTAX) score is merely based on angiographic features of dismal prognosis [2].

Therefore, this study aims to identify clinical, laboratory, echocardiographic and angiographic features that could refine available risk assessment schemes post-AMI. The ultimate goal is to develop a contemporary predictive risk model that includes clinical parameters, angiographic characteristics, biochemical biomarkers of systemic inflammation and echocardiographic myocardial work indices to identify high-risk patients in the acute phase and predict downstream cardiovascular complications.

## 2. Materials and Methods

### Study Design and Population

The ‘‘CLEAR-AMI’’ (ClinicalTrials.gov Identifier: NCT05791916) is a prospective, investigator-initiated, non-interventional study including patients with first AMI, ST-segment elevation myocardial infarction (STEMI) and Non-ST-segment elevation myocardial infarction (NSTEMI), hospitalized at the First Department of Cardiology of AHEPA University Hospital in Thessaloniki, Greece. All the patients undergo emergency coronary angiography in line with current guidelines [2]. The study adheres to the fundamental guidelines delineated in the Declaration of Helsinki [13] and the rules of good clinical practice, and has been approved by the Ethics Committee of the Aristotle University of Thessaloniki (reference number: 6.582/2022). The whole study design is presented in Figure 1.

This study aims to enroll a consecutive series of 500 patients presenting with first STEMI or NSTEMI and who are undergoing primary or emergency coronary angiography. A written informed consent is provided before enrollment for each eligible patient. Patients with a history of coronary artery disease, previous AMI or previous coronary intervention (percutaneous or surgical) will be excluded. Upon attaining the cohort of 500 patients, subgroup analyses will be conducted for NSTEMI and STEMI patients. The detailed eligibility criteria are described in Table 1.

## 3. Data Collection and Study Procedures

Demographic characteristics, baseline medical history, medication, prior diagnostic and therapeutic interventions, and clinical presentation of hospitalization will be recorded for all patients. In addition, patient laboratory data including complete blood count, biochemical, hormonal and coagulation mechanism control, high sensitivity troponin T levels (hs-cTNT) (admission and peak values) and N-terminal pro-B-type natriuretic peptide values will be collected within 24 h upon admission and during hospitalization. Moreover, the traditional lipid profile of the participants will be collected in addition to Lipoprotein A, and apolipoproteins B and A1. Special emphasis is placed on the assessment of inflammatory markers, including high-sensitivity C-reactive protein (hs-CRP), neutrophil-to-lymphocyte ratio (NLR), interleukin-6 (IL-6), soluble urokinase plasminogen activator receptor (suPAR), and admission glucose value, in order to evaluate stress-induced hyperglycemia. The prognostic impact of the investigated inflammatory markers (hs-CRP, IL-6, SuPAR) will be adjusted for potential cofounding variables such as concomitant autoimmune diseases and acute nosocomial infections as appropriate.

Clinical characteristics and risk scores, including Killip Class, GRACE risk score, TIMI-STEMI and ΤΙΜΙ-NSTEMI will also be recorded. Additionally, the coronary angiography of eligible patients will be assessed by two independent experienced interventional cardiologists who will be blinded to the demographic and clinical patient features. Angiographic data such as lesion characteristics, SYNTAX score and coronary dominance will also be taken into consideration.

All the eligible patients with AMI will be invited to visit the hospital one month post-AMI for a stress ECG test using the treadmill test. The test will be performed while the patient is on medication to assess the drugs’ effectiveness, their exercise capacity, and the chronotropic competence.

The primary endpoint will be all-cause mortality. The secondary endpoints will include (i) cardiovascular mortality (ii) heart failure rehospitalization and (iii) a composite of cardiovascular mortality, non-fatal acute myocardial infarction, unplanned PCI and heart failure hospitalization.

Artificial intelligence, specifically machine learning tools such as Extreme Gradient Boosting (XGBoost), will be used to identify clinical laboratory, echocardiographic and angiographic biomarkers with significant prognostic value and create potent diagnostic algorithms and predictive models. XGBoost stands as a prominently employed machine learning technique that is recognized for its exceptional efficacy and various functionalities, including regression, classification, and ranking quandaries [14]. It utilizes an iterative process of recursive binary partitioning to pinpoint the most advantageous division at each step, culminating in the development of an improved model [14].

All eligible patients with AMI will be actively encouraged to participate in a post-myocardial infarction exercise-based cardiac rehabilitation program as recommended by the current guidelines [2]. AMI patients will be encouraged to follow a personalized exercise program consisting of three sessions per week and supervised by a trainer under doctors’ directions. The aerobic and anaerobic exercises selected will be based on the age, gender, and physical status of each patient. The duration will initially be 30 min and the intensity will be low. Both the duration and intensity will be increased gradually according to the patients’ progress, aiming to exercise 5 times per week, 1 h per session with moderate intensity. The maximum heart rate obtained will be based on the stress ECG test that they will have in advance of the rehabilitation at 1 month post-AMI.

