The extent of inflammation, in the context of acute myocardial ischemia, is directly proportionate to infarct healing and the subsequent formation of scar tissue [29,30]. However, it is also well established that an exaggerated and persistent inflammatory response exerts detrimental effects on myocardial tissue, leading to exacerbated damage and ultimately contributing to worse clinical outcomes [31]. In AMI, the inflammatory response is accompanied by the secretion of various cytokines, including IL-6. IL-6, a cytokine of interest, exhibits pleiotropic effects, including protection of myocytes against oxidative stress. IL-6, along with hs-CRP and hs-cTNT, demonstrates an important prognostic role for adverse outcomes during the early phase following STEMI, and for MACE prediction during a long-term follow-up [32]. In a similar fashion, blood glucose has been independently associated with MACE prediction in STEMI patients characterized by stress-induced hyperglycemia (blood glucose on admission > 140 mg/dl), even in patients without a history of diabetes mellitus [33]. However, the association of inflammatory markers with novel echocardiographic parameters and their role in the assessment of the infarct and inflammatory burden, as well as in the prediction of MACE, are yet to be investigated.

In line with the hypothesis that there are a considerable number of pathways underlying atherosclerosis and AMI that remain to be discovered, this study aims to elaborate metabolomic and inflammatory biomarkers, such as the admission values of Lipoprotein A, Apolipoprotein A1 and B, suPAR and interleukin-6 (IL-6). The fundamental basis is that the metabolic and inflammatory characteristics of patients significantly contribute to the development of cardiovascular disease, and specifically coronary artery disease and AMI [33,34,35,36,37,38]. The prognostic roles and associations of these parameters will be assessed in this study. Furthermore, the integration of artificial intelligence techniques may facilitate the development of clinically significant polygenic risk scores [39,40], thereby offering potential advancements in risk prediction and patient management.

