## Figures and Tables

**Figure 1 jcm-12-05726-f001:**
[figure not shown]
Study design diagram. Clinical, echocardiographic and laboratory features of 500 consecutive AMI patients without a history of coronary artery disease, will be evaluated to determine outcome predictors. Abbreviations: STEMI, ST-segment elevation myocardial infarction; NSTEMI, Non-ST-segment elevation myocardial infarction; MACE, Major Adverse Cardiovascular Event.

**Table 1 jcm-12-05726-t001:** Inclusion and exclusion criteria of the “CLEAR-AMI Study”.

Inclusion Criteria	Exclusion Criteria
Age > 18 years Patients presenting with acute myocardial infarction (AMI) with or without ST segment elevation (based on the Fourth Universal Definition of Myocardial Infarction) Coronary angiography during hospitalization for AMI, in which at least one stenosis > 50% in a major epicardial coronary artery or a branch of at least 2 mm diameter	Not providing informed written consent Previous medical history of AMI Previous coronary revascularization Patients with a life expectancy < 1 year due to serious comorbidities Patients with limited echocardiographic acoustic window to perform analysis

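### Admission glucose is to measure stress hyperglycaemia, but neither the adjustment sentence nor the covariate rule guarantees that diabetes is in the model for glucose.

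*Protocol article*

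**What the plan says.** Section 3 (Data Collection and Study Procedures) gives special emphasis to a group of inflammatory markers. The last item in that list is "and admission glucose value, in order to evaluate stress-induced hyperglycemia". The next sentence sets out the adjustment: "The prognostic impact of the investigated inflammatory markers (hs-CRP, IL-6, SuPAR) will be adjusted for potential cofounding variables", with examples "such as concomitant autoimmune diseases and acute nosocomial infections as appropriate". Glucose is not among the three markers in the parenthesis, and diabetes is not among the example confounders.

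The same section states: "Demographic characteristics, baseline medical history, medication, prior diagnostic and therapeutic interventions, and clinical presentation of hospitalization will be recorded for all patients". Diabetes history should therefore be on file. Table 1 does not exclude diabetes.

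Section 3.2 (Statistical Analysis) plans univariable and multivariable logistic and Cox regression to find independent predictors. It restricts the multivariable models to covariates that are significantly associated with the endpoint on their own, with a two-sided threshold of 0.05. It also plans likelihood ratio tests for the incremental value of laboratory parameters over baseline models.

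Section 4 (Discussion and Expected Results) mentions a threshold when it summarises a cited study of STEMI patients: "stress-induced hyperglycemia (blood glucose on admission > 140 mg/dl), even in patients without a history of diabetes mellitus".

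**The concern.** A glucose reading at admission combines the acute response to the infarction with the patient's usual glucose level. In a patient with diabetes the second part can be large. Diabetes is also plausibly related to mortality, so it is the first confounder to control when admission glucose is read as a marker of stress or inflammation.

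The plan specifies the marker and the adjustment, and the two do not meet. The sentence that promises adjustment leaves glucose out, and the general model rule makes the entry of diabetes depend on a significance test in the same data. If diabetes misses that threshold while glucose passes it, the model reports glucose as an independent predictor with no account of diabetes. The association would then be labelled stress-induced hyperglycaemia although some or all of it may be chronic disease. The Discussion itself raises diabetes history when it discusses glucose, but the methods do not carry this over.

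**Working it through.** The plan gives no figure for this point, so there is nothing to reproduce. Two illustrations follow. Unless marked as taken from the article, every input is an assumption.

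**1. How large an association can diabetes alone produce?**

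Let d be the share with diabetes, h1 and h0 the shares above a glucose cut-off with and without diabetes, and R the mortality ratio for diabetes. Glucose is given no effect of its own. The cut-off is 140 mg/dl, borrowed from the study cited in section 4.

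- Diabetes share in the high-glucose group: sH = d·h1 / [d·h1 + (1−d)·h0]
- Diabetes share in the low-glucose group: sL = d(1−h1) / [d(1−h1) + (1−d)(1−h0)]
- Crude risk ratio: RR = [1 + (R−1)·sH] / [1 + (R−1)·sL]

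Middle inputs (d = 0.28, h1 = 0.80, h0 = 0.25, R = 1.7):
- sH = 0.224 / (0.224 + 0.180) = 0.554
- sL = 0.056 / (0.056 + 0.540) = 0.094
- RR = (1 + 0.7 × 0.554) / (1 + 0.7 × 0.094) = 1.388 / 1.066 = 1.30

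| d | h1 / h0 | R | sH | sL | RR |
|---|---|---|---|---|---|
| 0.20 | 0.70 / 0.25 | 1.5 | 0.412 | 0.091 | 1.15 |
| 0.28 | 0.80 / 0.25 | 1.7 | 0.554 | 0.094 | 1.30 |
| 0.30 | 0.80 / 0.20 | 2.0 | 0.632 | 0.097 | 1.49 |

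A second grid was run on the odds-ratio scale: diabetes in 20–40%, glucose above the cut-off in 80–90% with and 20–35% without diabetes, event risk 8% without diabetes, and an odds ratio for diabetes of 1.5–2.5. The crude odds ratio for high glucose was 1.15 to 1.90. With diabetes in the model it is 1.00 by construction.

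**2. How likely is diabetes to pass the univariable screen?**

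From the article: about 500 patients and 20% dropout, hence 500 × 0.8 = 400 evaluable; two-sided 0.05. With 28% diabetes this is 112 patients with and 288 without. Take an assumed event risk of 8% without diabetes, hence 8% × 1.7 = 13.6% with it.

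- Pooled risk = (112 × 0.136 + 288 × 0.08) / 400 = 0.0957
- Standard error under no difference = √[0.0957 × 0.9043 × (1/112 + 1/288)] = 0.0328
- Standard error under the assumed difference = √[0.136 × 0.864/112 + 0.08 × 0.92/288] = 0.0361
- Chance of passing = Φ[(0.056 − 1.96 × 0.0328) / 0.0361] = Φ(−0.23) = 0.41

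The same calculation for other event risks and for the three input sets above:

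| Event risk without diabetes | Low inputs | Middle inputs | High inputs |
|---|---|---|---|
| 5% | 17% | 28% | 46% |
| 8% | 23% | 41% | 65% |
| 10% | 27% | 49% | 76% |
| 15% | 38% | 68% | 92% |

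The odds-ratio grid gave 19% to 83%. Under many of these inputs the screen is as likely as not to leave diabetes out.

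**A limit on the first illustration.** In the odds-ratio grid, where glucose has no effect, crude glucose would itself reach significance with a chance of only 6% to 53%. In every setting that was below the chance for diabetes. The problem is therefore mainly a biased estimate and an unsafe label, less a near-certain false finding.

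**The case against.** The strongest reply has four parts.

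*Section 3 describes data collection, not analysis.* It does not say that glucose will be dichotomised, analysed alone, or left unadjusted. A reader might infer that a patient with diabetes and a glucose above 140 mg/dl will be counted as stress-hyperglycaemic. The article does not support that: the figure belongs to a cited study, and the plan adopts no cut-off. This part stands, and the point is limited accordingly. It does not depend on a cut-off, because continuous glucose is confounded by diabetes in the same way.

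*Multivariable models are planned.* A reader might infer that the study cannot separate an acute signal from diabetes. That is too strong. Diabetes history should be recorded for everyone, is a candidate covariate, and may enter. What remains is that its entry depends on a significance screen. The screen is a general rule affecting every marker, but for glucose the most obvious confounder is the one at risk.

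*The adjustment sentence is loosely worded.* The confounders are introduced as examples, and the parenthesis also omits the neutrophil-to-lymphocyte ratio, so it may be shorthand. That is possible. The open wording applies to the confounders, however, while the markers are given as a list of three.

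*A fuller protocol or analysis plan may settle this.* It may, and the absence of a detailed glucose definition from an article is not a fault. The point rests on two rules that the article does state and that, followed as written, can leave diabetes out.

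It is also tempting to set the 1.49 against the odds ratio of 1.5 used for the sample size. That comparison should not be pressed: one is a risk ratio and the other an odds ratio, and the sample size was based on studies of myocardial work indices, not glucose.

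**Conclusion.** The point holds in a limited form. Admission glucose is to be used to evaluate stress-induced hyperglycaemia in a cohort that does not exclude diabetes, and the stated rules do not guarantee adjustment for diabetes. Some of any association reported under that label may be chronic disease.

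The size is illustrative only. With no true glucose effect, a crude high-versus-low comparison could show a risk ratio of about 1.15 to 1.5. This rests wholly on assumed values for diabetes prevalence, glucose distribution and the mortality ratio, and on an unadjusted, dichotomised comparison that the plan does not prescribe. The chance that diabetes passes the screen also depends on an event rate that the article does not give.

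The harm lies in interpretation: claims of independent association and of a stress or inflammatory mechanism. In a model built purely for prediction, glucose may be useful whatever its cause, and this point does not touch that use.

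**What to change.** In section 3, add admission glucose to the markers whose prognostic impact is adjusted, and name known diabetes as a confounder for it. In section 3.2, state that:

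- known diabetes stays in every model for glucose, whatever its univariable p value;
- glucose is analysed as a continuous value;
- its association is also reported by diabetes status, or with a glucose-by-diabetes interaction, as a supporting analysis;
- glucose is interpreted as a stress response only after this adjustment.

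The change takes a few sentences and uses medical history already recorded for every patient. The cost is a somewhat wider interval for glucose, most of all within the diabetes strata of a cohort of about 500, which is why the stratified result should be supporting only. Undiagnosed diabetes would remain uncontrolled, and the report should say so.

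### The plan adjusts first-24-h inflammatory markers for hospital-acquired infection as a confounder, although such infection generally follows the sample, so the adjustment can remove part of the markers' prognostic association

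*Protocol article*

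**What the plan says.** Section 3 (Data Collection and Study Procedures) lists the inflammatory markers and then states that the prognostic impact of three of them, hs-CRP, IL-6 and suPAR, will be "adjusted for potential cofounding variables such as concomitant autoimmune diseases and acute nosocomial infections as appropriate".

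On when the markers are measured, the article says three things:

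- Abstract: "Their laboratory profile focusing on systemic inflammation is captured during the first 24 h upon admission".
- Section 4 (Discussion): the biomarkers of interest are described with the words "such as the admission values of Lipoprotein A, Apolipoprotein A1 and B, suPAR and interleukin-6 (IL-6").
- Section 3: the laboratory panel (blood count, biochemistry, hormones, coagulation, admission and peak troponin, NT-proBNP) "will be collected within 24 h upon admission and during hospitalization". The later sentence that lists the inflammatory markers gives no sampling time, except that glucose is the admission value.

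The Introduction gives the purpose of the planned model: "to identify high-risk patients in the acute phase and predict downstream cardiovascular complications".

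**The concern.** A confounder of a marker's association with death must be able to influence the marker value. Infection already present when blood is drawn can do that, and so can autoimmune disease. An infection acquired during the stay generally cannot, if the blood was drawn in the first 24 h. It lies after the marker in time and may lie on the path from a strong inflammatory response to death. Holding it constant then takes away whatever part of the marker's prognostic value runs through infection.

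Inflammation is one of the study's main themes, and the three markers named are the ones affected. An attenuated estimate could make a useful marker look weaker than it is. The adjusted estimate would also answer a question that cannot be asked at the bedside early on, because whether the patient will acquire an infection is not yet known.

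**Working it through.** **Step 1. Timing and role.** There are two ways to read the text.

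| If the marker is… | Can hospital-acquired infection confound it? | Agrees with Abstract and Discussion? |
|---|---|---|
| a first-24-h or admission value | Generally no; the infection comes later | Yes |
| a value from later in the stay | Possibly; an infection already present can raise it | No |

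Under the first reading the adjustment is wrong in kind. Under the second it could be defended, but the marker is no longer the one described in the Abstract and, for suPAR and IL-6, in the Discussion. Either way the wording needs to change.

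**Step 2. Size.** The plan has no figure to reproduce on this point. It gives no infection rate, no relation between marker and infection, and no effect of infection on death. All inputs below are assumptions.

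Model, with the marker *x* in SD units:

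- logit P(infection) = a + g·x
- logit P(death) = b + (ln OR_direct)·x + d·infection

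The death model is fitted without and with infection. Share of the log-OR removed = 1 − ln(OR adjusted) / ln(OR unadjusted).

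*Set A.* OR_direct 1.5, a = b = −2.5, 400,000 simulated patients; infection in 7.6% to 10.5%, death in 8.5% to 10.6%.

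| g (log-OR per SD) | d (log-OR) | OR unadjusted | OR adjusted | Share removed |
|---|---|---|---|---|
| 0 | 0.7 | 1.497 | 1.501 | 1 − 0.4061/0.4035 = −1% |
| 0 | 1.5 | 1.485 | 1.505 | 1 − 0.4088/0.3954 = −3% |
| 0.5 | 0.7 | 1.544 | 1.492 | 1 − 0.4001/0.4344 = 8% |
| 0.5 | 1.5 | 1.618 | 1.500 | 1 − 0.4055/0.4812 = 16% |
| 1.0 | 0.7 | 1.626 | 1.494 | 1 − 0.4015/0.4861 = 17% |
| 1.0 | 1.5 | 1.816 | 1.498 | 1 − 0.4041/0.5966 = 32% |

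With g = 0 the marker does not affect infection risk and nothing is lost. The small negative values reflect the fact that an odds ratio moves slightly when a risk factor unrelated to the marker is added.

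*Set B.* Infection in 8.5% to 9%; 2,000,000 simulated patients; OR_direct about 1.40, as the adjusted column shows.

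| Marker → infection OR per SD | Infection → death OR | OR unadjusted | OR adjusted | Share removed |
|---|---|---|---|---|
| 1.5 | 3 | 1.470 | 1.404 | 1 − 0.3393/0.3853 = 12% |
| 1.8 | 3 | 1.506 | 1.399 | 1 − 0.3358/0.4095 = 18% |
| 1.8 | 5 | 1.572 | 1.407 | 1 − 0.3415/0.4523 = 25% |

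In both sets the adjusted model returns the direct effect only. The loss is the part that runs through infection. For scale, section 3.2 sizes the study to detect an odds ratio above 1.5. In Set B the unadjusted value crosses that line in two of three scenarios, and the adjusted value in none.

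**The case against.** The strongest reply is that this is loose wording in a condensed article. The adjustment is qualified by *as appropriate*, and the authors may simply mean infection that could contaminate the measurement. Section 3.2 also admits only covariates that are significant at univariate analysis, so infection might never enter a model. And the loss is zero if early marker levels do not affect infection risk.

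The last point stands and sets the lower end of the range. The others soften the commitment without removing it. Hospital-acquired infection is still named as a confounder, the qualifier gives no rule for when it applies, and univariate significance says nothing about whether the infection preceded the sample.

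A reader might infer more than the article supports:

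- **That post-baseline data enter the final risk model.** The adjustment sentence concerns the association of three markers. The Introduction's list of model inputs does not include hospital-acquired infection, and recording serial laboratory values does not make them predictors.
- **That the laboratory timing is flatly contradictory.** The wording about collection during hospitalization is attached to the general panel, where a peak troponin requires repeat sampling. Doubt remains only for NLR, which comes from the blood count, and possibly for hs-CRP.
- **That immortal-time bias occurs.** This depends on time zero and on which values are used. The article states neither, and such detail commonly sits in the full protocol or analysis plan.
- **That follow-up should start when the echocardiogram is complete.** It may take place up to 48 h after admission, so this would drop earlier deaths from an all-cause mortality endpoint.

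**Conclusion.** The point holds in narrow form. As written, section 3 names a generally later event as a confounder of markers that the article elsewhere times to the first 24 h or to admission. This can attenuate the estimates for hs-CRP, IL-6 and suPAR; it does not necessarily do so.

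The size cannot be settled from the documents. It is about 0% of the log-OR when the marker has no effect on infection risk and roughly 12% to 25% in the Set B scenarios; the wider assumptions of Set A give 8% to 32% where such an effect exists. These figures rest on an assumed infection frequency of roughly 8% to 11% and on assumed effects of marker on infection and of infection on death. They show what could happen and do not estimate what will. The reasoning about timing does not depend on them.

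**What to change.** 1. In the section 3 adjustment set, replace acute nosocomial infections with *infection present at the time of sampling*. Autoimmune disease can stay.
2. Show later hospital-acquired infection only in a sensitivity analysis, for example as a time-updated covariate, and label it as such.
3. State in section 3 that the first-24-h value is used in the models for all inflammatory markers, including NLR and hs-CRP, so that it agrees with the Abstract.

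The cost is a change of wording and a date/time filter on laboratory and infection records. No new sampling is needed. The small downside is that later in-hospital marker values are not used in the main marker models; they can still be collected and described.
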